## Abstract

The proposed randomized controlled trial protocol will evaluate the effect of acupuncture treatment on the functional capacity (FC) and health-related quality of life (HRQOL) in chronic kidney disease (CKD) with glomerular filtration rate (GFR) category 5 (CKG G5) patients receiving maintenance dialysis. Patients undergoing hemodialysis (HD) from a dialysis center will be randomly assigned to experimental, placebo and control groups. In order to determine the difference between the same number of treatments performed three times or one treatment a week, experimental (verum acupuncture) and placebo (sham acupuncture) groups will receive a total of nine acupuncture treatments; however, both groups will be divided into subgroups A and B. The same selection of acupuncture points will be applied to both experimental subgroups and the placebo subgroups will receive acupuncture on non-acupuncture points. The results will be assessed by the 6-min Walk Test, Handgrip Test, 30-sec Sit-to-Stand and Kidney Disease Quality of Life-Short Form and will be held at baseline, after treatment and 12 weeks post-treatment follow up. This paper describes the rationale and design for a randomized, patient-assessor blinded controlled trial, which may provide evidence for the clinical application of acupuncture in CKG G5 patients undergoing HD.

## 1. Introduction

Over the last few decades, chronic diseases have become increasingly relevant and, according to the statistics, this type of disease is the leading cause of death worldwide and considered by the World Health Organization (WHO) to be the greatest threat to the health of the population in the 21^st^ century [1].

Chronic kidney disease (CKD) is considered a public health problem due to the increasing incidence and prevalence, as well as to high associated economic costs, substantially affecting the life of the patient and implying a significant burden on the health system [2,3]. Kidney Disease: Improving Global Outcomes (KDIGO) 2012 Clinical Practice Guideline for the Evaluation and Management of Chronic Kidney Disease defines CKD as abnormalities of kidney structure or function, present for more than 3 months, with implications for health and classified based on cause, glomerular filtration rate (GFR < 60 mL/min/1.73 m^2^ and albuminuria (AER ≥ 30 mg/24 h; ACR ≥ 30 mg/g (≥3 mg/mmol)) categories. Glomerular filtration rate (GFR) is generally accepted as the best overall index of kidney function and decreased GFR is associated with a higher risk of complications of CKD [4,5].

Although CKD etiology is diverse and due to diseases, such as glomerulopathies, polycystic kidney disease, autoimmune diseases, systemic infections, recurrent urinary tract infections, obstructive uropathies and neoplasms, CKD is most commonly associated with diabetes and hypertension, which are determining factors in the increase and prevalence of the disease [6]. Complications of decreased kidney function can lead to kidney failure (GFR < 15 mL/min/1.73 m^2^), the most advanced stage of CKD. Patients who have CKD with GFR category 5 (CKG G5) can only be treated by kidney replacement therapy (KRT), in particular peritoneal dialysis (PD), hemodialysis (HD), kidney transplantation (KT) and conservative kidney management [4].

The improvement in technologies and innovation around hemodialysis (HD) treatment has contributed to the increase in kidney failure prevalence due to the fact that patients survive longer on dialysis [7,8]. Patients undergoing HD suffer from several physical and emotional problems, have a complex and demanding treatment regimen, face a stressful and disruptive chronic illness with high impact on their quality of life [4,9,10] and have a significant decrease in functional capacity (FC) [11].

Traditional Chinese Medicine (TCM), recognized by the WHO and increasingly accepted in Western medicine as a therapeutic approach to the treatment of various diseases, is based on different concepts of etiopathogenesis, semiology, physiology and therapeutics. Scientific advances, especially in the field of neurosciences, have decisively contributed to the clarification and understanding of the neurobiological basis inherent in the acupuncture mechanisms of action [12,13].

Recent studies report early research for the application of TCM concepts and acupuncture in the field of nephrology. Examples include a study conducted by Paterno et al. (2008) suggested that there can be beneficial effects of electroacupuncture and moxibustion on CKD [14]; Kim et al. (2011) studied patients undergoing hemodialysis and receiving acupuncture treatment for their symptoms, and acupuncture seemed to be feasible and safe for symptom management [15]; Bullen et al. (2018) concluded that acupuncture during HD may contribute toward improvements in health-related quality of life [16]; Yu et al. (2017) evaluated the feasibility effect of acupuncture on renal function in patients with CKD and results suggested reduced creatinine levels and increased GFR [17].

Despite encouraging results, more scientific research will be required to expand understanding of the mechanisms responsible for positive action and of the therapeutic effects of acupuncture [18]. According to Kim et al. (2016), future high-quality randomized controlled trials are required to verify the safety and effectiveness in pre-dialysis patients with CKD and in those undergoing dialysis, to compare acupuncture with placebos and to verify whether intensive short-term acupuncture interventions or ongoing but less frequent treatments are advantageous for patients [19].

The fundamental questions guiding our entire research project are: What is the effect of TCM therapeutic strategies in the improvement of symptoms resulting from renal replacement therapy in CKG G5 patients undergoing HD? Does acupuncture have a positive effect on FC and health-related quality of life (HRQOL) in hemodialysis patients? If it does, are the results maintained over the long term? In addition, what is the effectiveness of short-term intensive interventions when compared to less frequent and prolonged interventions? Is it possible to integrate acupuncture into the dialysis care routine? Given our research project and the complexity of CKD, the objectives of this study are: (1) to assess the effect of acupuncture on FC and HRQOL in patients undergoing hemodialysis; (2) to evaluate the specific effects of acupuncture as compared to a placebo; (3) to evaluate short- and long-term effects of acupuncture; (4) to determine the difference between short-term intensive and ongoing but less frequent acupuncture treatments; (5) to assess the feasibility of integrating acupuncture in dialysis care.

## 2. Materials and Methods

### 2.1. Study Setting

A parallel-group patient-assessor blinded randomized controlled trial will be conducted in a single center and according to the trial flow chart procedure presented in Figure 1. The recruitment and the whole treatment process will be carried out at the Hemodialysis Center of TECSAM—Tecnologia e Serviços Médicos, SA, in Mirandela, Portugal. The research protocol and informed consent procedure were approved by the Ethics Committee of Centro Hospitalar Universitário do Porto/Instituto Ciências Biomédicas Abel Salazar (registered number 2019/CE/P026_P304/2019/CETI), and is an integral part of the research project of the Doctoral Program in Biomedical Sciences of ICBAS School of Medicine and Biomedical Sciences, Oporto University, Portugal. This trial was registered at ClinicalTrials.gov (NCT05362643). The study protocol will be reported in accordance with the Standard Protocol Items: Recommendations for Interventional Trials (SPIRIT) guidelines [20].

### 2.2. Recruitment

An advertisement will be posted on the clinic notice board and if all study criteria are met, volunteer patients who are receiving treatment at TECSAM Hemodialysis Center will be invited to participate.

### 2.3. Eligibility Criteria

Inclusion and exclusion criteria will be applied during the participant selection process and potentially eligible participants will be identified by a nephrologist and through screening of their TECSAM Hemodialysis Center patient medical records.

This trial will include male and female patients, age 18 years or older, who have been receiving regular hemodialysis treatment for more than 3 months, undergoing sessions 3times a week, at 4 h per session, and who are in a medically stable condition.

Patients who refuse to participate in the study or who have a clinical indication that prevents their participation in the study, and patients with other comorbidities, such as poorly controlled malignant hypertension, unstable angina, uncontrolled diabetes mellitus, cerebrovascular failure with recurrent syncope, uncontrolled heart failure, severe mental illness or cognitive impairment, will be excluded. Those with other relevant circumstances, including the inability to practice physical exercise, having undergone acupuncture treatment in the past two weeks, having experienced a known hypersensitivity reaction and/or other side effects after acupuncture treatment, and displaying an inability to cooperate with the procedures inherent to the application of the procedure, will be also excluded from the study.

### 2.4. Randomization and Allocation

After screening for eligibility, a written informed consent form containing an explanation of the objectives and procedures for the research project’s implementation will be obtained from each individual who agrees to participate, in compliance with the revised version of the Declaration of Helsinki and the Oviedo Convention. The procedure will be performed by an independent assessor, with each one assigned an anonymous code. Participants will be randomly allocated in a 1:1:1 ratio and assigned to the experimental group (verum acupuncture), the placebo group (sham acupuncture) or the control group (non-acupuncture) following simple randomization procedures employing a computerized random number list. The randomization sequence will be created using Microsoft^®^ Excel^®^ for Microsoft 365 MSO Microsoft, Washington, USA by an independent researcher who will prepare the assignments in opaque envelopes and take charge of concealing the allocation sequence.

After the random assignment of the participants into the three groups and regarding the frequency of treatment, the first 12 randomized patients in the verum acupuncture (VA) and sham acupuncture (SA) groups will receive treatment 3 times a week, and the remaining 12 will receive treatment once a week, with a total of 9 treatments for each subgroup.

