### 3.4. Statistical Analysis and Sample size

Demographic and clinical data for each group at baseline will be compared using Fishers’ Exact Test (categorical variables) and one-way ANOVA (continuous variables). Two-way repeated-measures ANOVA with interaction between time (baseline, 3 weeks, 9 weeks and follow-up period 12 weeks after treatment) and group will be used to assess the effect of the treatment. Differences over time within each group and subgroup will be assessed with repeated-measures ANOVA, and differences among groups at each moment will be evaluated with one-way ANOVA. A significance level of 5% will be used; differences will be considered statistically significant for *p*-value < 0.05. Statistical analysis will be performed with IBM SPSS Statistics software, version 27.0, IBM, New York, NY, USA [33].

For the sample size, a minimum of 20 patients in each group (experimental, placebo and control groups) was estimated to achieve a small to medium effect size (f = 0.19) [34] in the two-way repeated-measures ANOVA, with a statistical power of 80% and a significance level of 5%. Sample-size calculations were carried out using G*Power V.3.1 [35]. Assuming a possible dropout rate of 15%, a minimum of 24 patients will be randomly selected for each group. In the experimental and placebo groups, half of the patients (*n* = 12) will be placed in subgroup A, with three acupuncture sessions per week over 3 weeks, and half (*n* = 12) will be placed in subgroup B, with one acupuncture session per week over 9 weeks.

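### Simple 1:1:1 randomisation does not guarantee the fixed sizes (24 per arm, 12 per frequency subgroup) that the protocol relies on

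*Protocol article*

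**What the plan says.** Section 2.4 of the protocol article: "Participants will be randomly allocated in a 1:1:1 ratio", "following simple randomization procedures employing a computerized random number list". It mentions no blocking, stratification or cap on an arm. An independent researcher prepares the sequence in Excel and conceals it in opaque envelopes.

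The next paragraph of Section 2.4 gives the earliest twelve patients in each of the verum and sham arms three sessions a week, "and the remaining 12 will receive treatment once a week". That sentence is true only if each of those arms holds exactly 24.

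Section 3.4 sets the numbers: "a minimum of 20 patients in each group (experimental, placebo and control groups) was estimated" for 80% power at the 5% level, raised for 15% dropout so that "a minimum of 24 patients will be randomly selected for each group". It repeats n = 12 for each frequency subgroup. The overall total is not printed; 3 × 24 = 72 is implied.

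**The concern.** Under simple randomisation each patient is assigned independently, so arm sizes are random. The article states both this method and sizes that need a restricted method. This is a conflict between two stated things, not a detail left to a fuller document.

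Two things are at stake. One is the margin of 24 over 20 that Section 3.4 builds in for dropout, which chance imbalance can use up before anyone drops out. The other is the frequency comparison, which is objective 4 in the Introduction and carries a directional expectation in the Discussion. The three-times-weekly subgroup is filled first, so the once-weekly subgroup absorbs all the chance variation in its arm. Whoever builds the list must decide how to reconcile method and sizes, and the article does not say how.

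**Working it through.** **Inputs.** From Section 2.4: simple randomisation, 1:1:1, 12 + 12 in verum and sham. From Section 3.4: 20 per arm, f = 0.19, power 80%, alpha 5%, dropout 15%, 24 per arm. Assumed: randomisation stops at 72; for power, correlation between repeated measures ρ = 0.5 and sphericity, neither of which is stated.

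**The plan's own figures.** Take the within-between interaction in a repeated-measures ANOVA, with λ = f²·N·m/(1 − ρ), df1 = (k − 1)(m − 1), df2 = (N − k)(m − 1), and k = 3 groups.
- With m = 3 measurements, the smallest N reaching 80% is 58, rounded to 60 for equal arms: 20 per arm. At N = 60, λ = 0.0361 × 60 × 3 / 0.5 = 13.0 and power is 0.819.
- Dropout: 20 / 0.85 = 23.5, rounded up to 24.

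Both stated figures are reproduced under these assumptions.

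**Arm sizes under simple randomisation of 72.**
- SD of one arm's size: √(72 × 1/3 × 2/3) = 4.0.
- P(exactly 24/24/24) = 72! / (24!³ × 3⁷²) = 0.0114. Verum and sham both being 24 forces the control arm to 24, so the 12/12 split in both arms fails with probability 98.9%.
- P(a given arm < 20) = 0.1293. Three times this is 0.388; removing the overlap in which two arms are both short gives P(at least one arm < 20) = 0.3806. One million simulated allocations also gave 0.381.
- Once-weekly subgroup = arm size − 12. The 2.5th and 97.5th percentiles of the arm size are 16 and 32, so the subgroup's 95% range is 4 to 20.
- P(once-weekly subgroup < 8 in verum or sham), which is the same as verum or sham < 20: 25.6%.

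**Effect on the frequency comparison within an arm.** The standard error of a difference is proportional to √(1/n_A + 1/n_B), with equal variances and before dropout.
- 12 v 12: √(1/12 + 1/12) = 0.408 SD.
- 12 v 4: √(1/12 + 1/4) = 0.577 SD, 41% larger.
- 12 v 20: √(1/12 + 1/20) = 0.365 SD, 11% smaller.

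**Effect on the overall test** (85% completers, m = 3, ρ = 0.5). Mean power over simple allocations is about 0.819, against 0.828 with balanced arms. Some 27% to 29% of allocations fall below 80%, depending on the assumed pattern of group means. With the four time points listed in Section 3.4, the means are about 0.884 and 0.893, and 1.5% to 2.7% fall below 80%.

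**The other ways to read the text.**
- *Recruit until every arm has 24.* No arm falls short. But the chance that some arm is still under 24 is 98.9% at 72 patients, 43% at 84 and 9% at 96, so the total is open-ended. The other arms overshoot, and twelve remaining patients in both verum and sham is again a matter of luck.
- *A shuffled list with 24 slots per arm.* All sizes hold, but this is restricted randomisation, and the method is misnamed.

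**The case against.** The strongest reply is that the 38% belongs to one reading only: independent draws that stop at 72, a total the article never prints. Section 3.4 calls 24 a minimum; if that is honoured, no arm can be under 20 at randomisation. The 1:1:1 ratio and the exact twelves also fit a shuffled fixed list, and Sections 2.4 and 3.6 are compatible with allocating a recruited pool in one go. This stands: the probabilities are conditional and must be labelled so. It does not remove the conflict, because on each reading some part of the printed text is wrong.

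A second reply is that an arm under 20 is a weak measure of harm. With 24 per arm fixed and independent 15% dropout, at least one arm would still have fewer than 20 completers in 63.7% of trials, against 91.5% under simple randomisation. This also stands. Restriction removes the avoidable part only, and the mean power loss is about one point.

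A reader might infer that late assignments will be forced to reach 24 and so become predictable or biased. The documents do not support that. Nothing says the list will be overridden, and an independent researcher holds the concealed sequence. It is a risk if staff improvise, not something the plan provides for.

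**Conclusion.** The point holds as a conflict between the stated method and the stated sizes. Under simple randomisation, 24 per arm and 12 per subgroup are not guaranteed. If 72 patients are allocated independently, 24/24/24 occurs with probability 1.1%, some arm is below 20 before dropout with probability 38%, and a once-weekly subgroup has a 95% range of 4 to 20. These figures rest on the implied total of 72 and on taking *simple* literally.

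Two stronger conclusions do not follow. It is not that the sizes cannot occur, only that nothing secures them. Nor is the trial shown to be materially underpowered for its overall test: the average loss is about one point, under an assumed correlation of 0.5 and three measurements. The harm lies mainly in the arm sizes and in the 12 v 12 frequency comparison, where a poor draw can raise the standard error by about 40%.

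**What to change.** In Section 2.4, replace simple randomisation with restricted randomisation that yields exactly 24/24/24 at 72, and print the total of 72. Use permuted blocks whose sizes are multiples of 3, in random order, with the number of blocks of each size fixed so that they sum to 72. For example, six blocks of 6 and four of 9 give 36 + 36 = 72, and 6 × 2 + 4 × 3 = 24 per arm. The constraint matters: if block sizes of 6 and 12 were chosen freely with equal chance, only about 67% of lists would end on a block boundary at 72. Conceal the block sizes from enrolling staff and from the practitioner, who knows each patient's arm.

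If the authors already hold a fixed 24/24/24 list, describing it correctly is enough. If they mean to recruit beyond 24 per arm, the sentence on the twelve remaining patients must be reworded as well.

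The cost is one sentence and a new list, made before the first envelope is opened, with slight predictability at block ends. By comparison, keeping simple randomisation would take about 87 patients to bring the chance of an arm below 20 under 5% (6.6% at 84, 4.0% at 87), and the 12/12 split would still not be secured.

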### 2.5. Blinding

The participants, the outcome assessor, the statistician and the Traditional Chinese Medicine practitioner will be blind to the allocation. Regarding the intervention itself, due to its specific nature, only the Traditional Chinese Medicine practitioner will not be blind to the verum acupuncture, sham and non-acupuncture groups.

To assess the effectiveness of the blinding, after the treatment, a questionnaire will be administered to ask the participants in the VA and SA groups what sort of acupuncture treatment (verum or sham) they believe they received. This question will allow the calculation of the James Blinding Index (BI) [21,22].

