### 2.6. Intervention

The experimental (verum acupuncture) and placebo (sham acupuncture) groups will receive 9 acupuncture treatments. Both groups will be divided into two subgroups with a different treatment frequency: subgroup A will receive 3 acupuncture sessions per week over 3 weeks; and subgroup B will receive 1 acupuncture session per week over 9 weeks. The same selection of acupuncture points, identified according to the method of point location issued by the WHO [23], will be applied to both experimental subgroups A and B. Placebo subgroups A and B will receive acupuncture at the same non-specific acupuncture points. Details of the acupuncture intervention will be described according to the revised Standards for Reporting Interventions in Clinical Trials of Acupuncture (STRICTA) 2010 Checklist [24], as listed in Table 1.

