## 4. Discussion

The protocol described above refers to a parallel-group patient-assessor blinded randomized clinical trial planned to assess the effect of acupuncture compared with placebo-sham acupuncture and non-acupuncture groups. Therefore, it was designed following the Standards for Reporting Interventions in Clinical Trials of Acupuncture (STRICTA) [24] and reported with the Standard Protocol Items: Recommendations for Interventional Trials (SPIRIT) guidelines [20].

CKD is a debilitating disease, and standards of medical care involve aggressive monitoring for signs of disease progression and early referral to specialists for dialysis or possible renal transplant [36]. As kidney disease progresses, patients often experience a variety of symptoms. The initiation of dialysis can have a variable effect on quality-of-life measures and on the alleviation of uremic signs and symptoms, such as anorexia, fatigue, cognitive impairment, depressive symptoms, pruritus and sleep disturbance [37].

HRQOL has been widely accepted as a valid marker of treatment outcomes and mortality for patients with chronic diseases [38]. Hemodialysis negatively impacts the HRQOL of patients, affecting their physical, functional, metabolic, social and mental conditions, with a high impact on functional capacity when compared to healthy individuals [39,40,41].

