Many pharmacological interventions for people with CKD have known risks of adverse events and, according to the literature, acupuncture is commonly used in symptom management for chronic diseases as well as in palliative care [42]. However, the safety and efficacy of acupuncture for people with CKD remains largely unknown. Considering the aims of our study, we expect that verum acupuncture compared to sham acupuncture and non-acupuncture will improve the functional capacity of hemodialysis patients, as evidenced by an increase in the distance walked on the 6MWT and an increase in scores for quality of life. In addition, we expect an increase in handgrip strength and an improvement in peripheral muscle strength. According to Kim et al. (2016), there was low-quality evidence of the short-term effects of manual acupressure as an adjuvant intervention for fatigue, depression, sleep disturbance and uremic pruritus in patients undergoing regular hemodialysis [19]. Under this assumption, this study protocol was designed to check the effect of acupuncture after treatment and at 12 weeks post-treatment. In this way, we expect that the effect of acupuncture will be maintained in the follow-up period.

Some studies, especially in the pain field, suggest that three treatments per week obtain better results than one treatment per week [43,44]. We also expect to see better results with more intensive interventions compared to less frequent and prolonged interventions.

Following review of the literature and to the best of the authors’ knowledge, there are currently no comparable studies. Therefore, our trial seems to be an innovative study for exploring the effect of acupuncture and the frequency of treatment on improving FC and HRQOL in patients undergoing HD. Furthermore, supported by only a few clinical cases reported (personal data) prior to the design and development of the research project, it is possible to predict efficacy and the advantages of integrating acupuncture treatments into routine hemodialysis as a complementary therapy to conventional treatments.

Despite fulfilling strict methodological criteria, it is possible to identify limitations in our study protocol. First, the sample size; second, the TCM practitioner performing the acupuncture treatment will not be blinded due to the nature of the intervention; third, comorbidities inherent to chronic kidney disease may lead to a high dropout rate during the follow-up period.

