	(6b) Precise description of the control or comparator. If sham acupuncture or any other type of acupuncture-like control is used, provide details as for Items 1 to 3 above.	The placebo group (sham acupuncture) will receive a total of 9 acupuncture treatments, however, will be divided into subgroups A and B. Placebo subgroup A will receive three acupuncture sessions per week over 3 weeks and subgroup B will receive one a week for 9 weeks. Manual acupuncture will be performed as superficial needling (5 mm depth) at non-acupuncture points without an attempt to achieve a *De qi* sensation and without stimulation, lasting 25 min, using a sterilized stainless-steel needle (0.25 × 25 mm; Tewa, asia-med GmbH, [name]).The control group (waiting list) will not receive any acupuncture treatment during the study period. **List of Non-Acupuncture points used and their location** In the present study, the non-acupuncture points selected will be the points located on the non-meridian but near the acupuncture points described above. Non-Acupuncture point 1 (NA1) Located near KI3 (*Taixi*). On the posteromedial aspect of the ankle, at the midpoint of KI3 (*Taixi*) and (*Fuliu*). KI7 (*Fuliu*) is located on the posteromedial aspect of the leg, anterior to the calcaneal tendon, 2 *cun* superior to the prominence of the medial malleolus. Non-Acupuncture point 2 (NA2) Located near SP6 (*Sanyinjiao*). On the leg, at the midpoint of the medial side of the tibia, 1 *cun* distal from SP6 (*Sanyinjiao*). Non-Acupuncture point 3 (NA3) Located near ST36 (*Zusanli*). On the anterior aspect of the leg, at midpoint of ST37 (*Shangjuxu*) and the Gallbladder Meridian. ST37 (*Shangjuxu*) is located on the anterior aspect of the leg, on the line connecting ST35 with ST41, 6 *cun* inferior to ST35, on the tibialis anterior muscle. Non-Acupuncture point 4 (NA4) Located near HT7 (*Shenmen*). On the wrist, at the transverse crease of the wrist, at the midpoint of HT7 (*Shenmen*) and PC7 (Daling), between the Pericardium Meridian and the Heart Meridian. Non-Acupuncture point 5 (NA5) Located near CV4 (*Guanyuan*). On the lower abdomen, 1 *cun* lateral from CV6 (*Qihai*). CV6 (*Qihai*) is located 1.5 *cun* inferior to the center of the umbilicus, on the anterior median line.

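### Participant blinding is claimed across all three groups, but with a waiting-list control it is possible only between verum and sham acupuncture

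*Protocol article*

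**What the plan says.** Section 2.5 opens with "The participants, the outcome assessor, the statistician and the Traditional Chinese Medicine practitioner will be blind to the allocation". The next sentence turns to the intervention itself and says that "only the Traditional Chinese Medicine practitioner will not be blind to the verum acupuncture, sham and non-acupuncture groups". Section 4 repeats, as a limitation, that "the TCM practitioner performing the acupuncture treatment will not be blinded due to the nature of the intervention". It lists no limitation about participants.

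The Abstract and Section 2.1 describe the trial as patient-assessor blinded. Section 4 ties the label to both comparators: "parallel-group patient-assessor blinded randomized clinical trial planned to assess the effect of acupuncture compared with placebo-sham acupuncture and non-acupuncture groups".

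On the arms, Section 2.4 states that "Participants will be randomly allocated in a 1:1:1 ratio", to verum, sham and control. Table 1, item 6b, says of the third arm: "The control group (waiting list) will not receive any acupuncture treatment during the study period". Within verum and sham, Section 2.6 says that "subgroup A will receive 3 acupuncture sessions per week over 3 weeks; and subgroup B will receive 1 acupuncture session per week over 9 weeks".

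Blinding is checked only by a post-treatment questionnaire (Section 2.5) that will "ask the participants in the VA and SA groups what sort of acupuncture treatment (verum or sham) they believe they received". The answers feed the James Blinding Index.

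**The concern.** A patient who is placed on a waiting list and never needled knows the assignment. A patient who is needled knows that he or she is not a control. The text nevertheless presents participants as blind to the non-acupuncture group, and nothing elsewhere in the article limits the label to verum against sham.

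What is at stake is how the results can be read. Section 3.1 makes HRQOL by KDQOL-SF a primary outcome alongside the 6-minute walk. KDQOL-SF is filled in from the patient's own perception, and walking distance can depend on effort. A blinded assessor does not remove the patient's expectations from either. Section 4 expects verum to do better than both sham and non-acupuncture, and Section 5 expects evidence of efficacy. Under an unrestricted blinding label, a difference from the waiting list could be read as if expectation had been controlled.

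**Working it through.** No figure in the plan depends on blinding, so the check is mainly a comparison of the texts. The one count needed comes from the sample-size text.

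**Planned numbers.** Section 3.4 gives 20 per group and 15% dropout. 20 / (1 − 0.15) = 23.5, rounded up to 24, which reproduces the stated 24 per group. Three groups give 3 × 24 = 72. The waiting list is 24 / 72 = 33%, and the two needled groups are 48 / 72 = 67%.

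**What is claimed about participants.** The first sentence of Section 2.5 says that they are blind to the allocation. The second names verum, sham and non-acupuncture as the groups concerned and exempts only the practitioner. Together these assert participant blinding for all three groups.

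**What the design allows, by contrast and role.**

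| Contrast | Participants | Practitioner during treatment | Assessor and statistician |
|---|---|---|---|
| Verum v sham | can be masked | not blinded | stated blinded (Section 3.6) |
| Verum v waiting list | cannot be masked | not blinded | stated blinded |
| Sham v waiting list | cannot be masked | not blinded | stated blinded |
| Schedule A v schedule B | aware of schedule | not blinded | stated blinded |

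Three groups give three pairwise contrasts, and two of them involve the waiting list. Participants can be masked in one of the three.

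**Would the blinding check reveal this?** No. It questions only needled patients and offers only verum or sham as answers. It is silent on the contrasts with control. It does have a use for verum against sham, where Table 1 gives the two procedures different depth, sensation sought and stimulation, so that masking there is intended but not assured.

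**Does it reach the analysis?** Section 3.4 tests a time-by-group interaction over the three groups and uses one-way ANOVA among groups at each time. Suppose, for illustration, that the mean change is d in verum, d in sham and 0 on the waiting list. Then verum − sham = d − d = 0, while verum − control and sham − control both equal d. The three-group interaction is then non-null although the masked contrast shows nothing. A significant overall test can therefore come entirely from the arm whose participants are not blinded.

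**The case against.** The strongest reply is that the design is fully disclosed. The control is called a waiting list, the blinding questionnaire is limited to the needled groups, and the second objective in Section 1 already ties specific effects to the comparison with placebo. On that view one qualifying clause is missing, and an informed reader would supply it. Disclosure of the arms does stand, and so does the point about the second objective. But Section 2.5 includes the non-acupuncture group by name, Section 4 attaches the label to both comparators, and the limitations name only the practitioner. The text asserts what the reader is asked to discount.

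Four stronger readings may tempt a reader and are not supported:

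- **That the practitioner statements are a serious contradiction.** Taken alone, the two sentences of Section 2.5 conflict. Section 3.6 keeps the practitioner from patient data until allocation is complete, and Section 4 admits that the practitioner is unblinded. The first sentence can thus be read as concealment up to assignment. It needs clarifying, no more.
- **That the protocol falsely claims blinding to weekly schedule.** Section 2.5 speaks of the three groups and never of frequency. Patients know their schedule, which is worth stating, but no claim is broken. Within each schedule the verum/sham mask can still hold.
- **That blinding fails for every role outside verum v sham.** Section 3.6 says that the head nurse who assesses outcomes and the statistician are unaware of allocation, and nothing in the article refutes this for any contrast.
- **That the contrasts with control are open-label.** With a blinded assessor, that term is wrong.

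It is also fair to say that 24 of 72 is a count. It gives no size of bias.

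**Conclusion.** The point holds for participants. The protocol ascribes to them a blinding that the design cannot provide for the two contrasts with the waiting list, and no part of the article corrects it. Participant blinding is possible only for verum against sham.

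By plan this concerns 24 of 72 participants who know their arm, 48 who know that they are not controls, and two of the three pairwise group contrasts. The count uses the planned size; simple randomization may give somewhat different numbers. The conclusion assumes that waiting-list patients receive no mock procedure, as Table 1 describes. How far expectation would shift KDQOL-SF or walking distance cannot be derived from the article.

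A waiting-list arm is a legitimate choice. The fault lies in how it is described and in what could then be concluded from the three-group test. No sample size, procedure or planned test has to change, but the correction should be made because a primary outcome is self-reported.

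**What to change.** Restate blinding in Section 2.5 by role and by contrast, and align the Abstract, Section 2.1 and Section 4:

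- Participants: blind to verum v sham only; not blind to control status; aware of their weekly schedule.
- Practitioner: not blinded during treatment. Reword the first sentence of Section 2.5 to agree with Sections 3.6 and 4, for example by limiting it to concealment before assignment.
- Outcome assessor and statistician: blinded, as Section 3.6 states.

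Add participant unblinding to the limitations in Section 4. State that conclusions on specific effects or efficacy, above all for KDQOL-SF, rest on the verum v sham contrast and not on the three-group test alone. Report the contrasts with the waiting list and between schedules A and B as participants not blinded, assessor blinded.

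The cost is a slightly less favourable description of the design. No patients, visits or measurements are added.
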